#### Health related outcomes

Body weight will be assessed at all measurements using calibrated electronic flat scale (SECA 877, SECA, Burmingham, UK) with accuracy to the nearest 0.1 kg. Participants will be allowed to wear normal clothes, but will be asked to remove any heavy items of clothing (e.g. jackets), their shoes and any items in their pockets. Body height will be measured only at baseline after participants have removed their shoes using a portable stadiometer (SECA 206, SECA, Birmingham, UK) with accuracy to the nearest millimetre. BMI will be calculated as weight in kilograms divided by the square of height in meters (kg/m^2^).

Waist circumference will be measured twice at the level midway between the lowest ribcage and the iliac crest using a non-expendable tape (SECA 201, SECA, Birmingham, UK) with accuracy to the nearest 0.1 cm. Participants will be asked to remove their shirts. If the first two waist measurements differ by ≥0.5 cm, a third measurement will be done. The mean circumference will be calculated from the (two nearest) measures.

Musculoskeletal symptoms will be assessed based on the modified Nordic Musculoskeletal questionnaire (SNQ) [27]. Participants are asked if they experienced any pain or discomfort in the following anatomical regions: 1) neck, shoulders or upper back; 2) arms, wrists or hands; 3) lower back; 4) hips, thighs, knees, ankles or feet, in the past three months (no; yes, sometimes; yes, regularly; yes, prolonged). If participants answer yes, they are asked to indicate the maximum intensity of the worst symptoms on an eleven-point scale (‘0’ no pain – ‘10’ extremely painful).

Difficulties workers experience in recovering from work-related exertion will be assessed by using the Need For Recovery scale (NFR) [28]. The NFR comprises of eleven items with dichotomous answering categories (yes/no). A score is calculated by adding all the scores of the individual items and transforming these into a scale from 0 to 100. Higher scores indicate a higher need for recovery after work. The NFR has shown favourable test-retest reliability and sensitivity to detect change [29].

Vitality will be assessed by using the Vita-16© TNO questionnaire [30], which consists of the following three core dimensions: energy, motivation and resilience. Energy is characterized by feeling energized and full of pep, motivation is defined by setting goals in life and putting effort into achieving these goals, and resilience is characterized by the ability to cope with daily life problems and challenges. These three dimensions are measured with a 16-item questionnaire on a seven-point Likert scale (‘1’ hardly to ‘7’ always), which has been found valid and reliable in a Dutch adult population [30].

Quality of Life will be assessed with the EQ-5D-5 L questionnaire [31, 32]. Participants are asked to rate their mobility, self-care, usual activities, pain/discomfort, and anxiety/depression on a five-point scale (i.e. no problems, slight problems, moderate problems, severe problems, or extreme problems). They are also asked to rate their today’s health on a scale ranging from zero (worst health imaginable) to one hundred (best health imaginable).

#### Socio-demographic characteristics

At baseline, age, gender, ethnicity, marital status, number of children living in their household, household composition, education level, household income, employment status (i.e. length of tenure, working hours, job classification, overtime hours and number of days working from home), postal code and possible co-interventions (e.g. participation in other lifestyle or health programs, access and use of sit-stand desks or cycling workstations) will be assessed.

### Economic evaluation

Work absenteeism and presenteeism will be self-reported and measured using iMTA Productivity Cost Questionnaire (iPCQ) [33] at three and twelve months. The iPCQ questionnaire measures on both time points sick leave and productivity losses while being at work but not functioning optimally. Work absenteeism will also be assessed using company records.

Healthcare utilization will be assessed using an adapted version of the iMTA Medical Cost Questionnaire (iMCQ) at three and twelve months. This questionnaire will include the number of visits to the general practitioner, allied health professionals or complementary healthcare providers, medication use, the number of ambulatory visits at a hospital or other health care organizations, and admissions to a hospital or other health care organizations. Healthcare utilization will also be assessed using company records for those with insurance at the insurance company.

The costs for the delivery of the program will be calculated using a bottom-up approach using costs reported by the insurance company (i.e. preparation, coordination and administration, recruitment of participants, implementation and delivery of the program, and materials including Activator, sit-stand desks, cycling workstations and office balls), and the participating university (i.e. preparation and start-up, and materials).

Dutch standard costs will be used to value health care utilization and productivity losses [34] . Patient and family costs other than informal care will be valued using self-reported prices. Medication costs will be estimated using prices of the Royal Dutch Society for Pharmacy. For the valuation of absenteeism from paid work, the friction cost approach will be used.

### Process evaluation

An extensive process evaluation is embedded in this study to investigate processes that are necessary for sustainable implementation of the Dynamic Work intervention, the way in which the intervention affects outcomes, and facilitators and barriers for adoption, implementation and continuation. The mixed-method design of this process evaluation has been informed by MRC guidance on process evaluation of complex interventions [35] and builds on previous extensive process evaluations [16, 36, 37]. Data will be gathered from participants, heads of department/team managers, occupational physiotherapists, and Dynamic Work coordinators. Researchers will keep field notes in which relevant information is reported of phone calls, email and measurement observations. Furthermore, usage data from the Activator app will be collected remotely (e.g. logs of data upload and error reports). Table 2 presents an overview of the process evaluation objectives and methods used ordered in the domains context, implementation and mechanism of impact.

**Table 2 Tab2:** Overview of process evaluation objectives and methods used

	Q-B	Q-3M	Q-12M	FG-3M	INT-w	Activator	AR	Logbook	INT-OP- 12M	FG-HD/TM-12M	INT-DWc-12M	FN
CONTEXT												
Reach												
Characteristics of participating departments (e.g. size, facilities and work content).								X		X	X	X
Characteristics of occupational physiotherapist (e.g. background, demographics, and experience).									X			
Characteristics of participants (e.g. demographics and health risk profile).	X											
Facilitating factors and barriers to delivery of Dynamic Work at departments												
Perceived barriers and facilitators for implementation, attractiveness to participate, successes and failures regarding recruitment and intervention delivery, intention for continuation, and future activities.									X	X	X	
IMPLEMENTATION												
Recruitment												
Sources and procedures for recruitment of departments, and reported reasons for (non-)participation.										X	X	X
Sources and procedures for recruitment of occupational physiotherapists to deliver Dynamic Work in participating departments.									X		X	X
Sources and procedures for recruitment of participants, and reported reasons for (non-)participation and withdrawal from the study.	X			X	X					X	X	X
Delivery												
Total number of installed sit-stand desks and cycling workstations, number of delivered plenary and on-site counselling sessions, number of occupational physiotherapist consultations, and number of distributed Activators and self-help program booklets (dose delivered).						X		X			X	X
Participation in the Dynamic Work intervention (e.g. number of attended sessions, coach consultations and use of sit-stand desk, cycling workstation, Activator and self-help program booklet) (dose received).		X	X	X		X	X	X				
The extent to which occupational physiotherapists delivered the face-to-face session with the head of the department/team managers, the plenary Dynamic Work sessions and on-site department counselling sessions as intended (fidelity).								X				
MECHANISMS OF IMPACT												
Experiences of the Dynamic Work intervention and which elements were most useful												
Head of department/team manager and coordinator views and experiences of adopting and implementing the Dynamic Work intervention.										X	X	X
Occupational physiotherapists’ experience with the Dynamic Work intervention and view on essential elements in supporting participants to make behavioural change.									X			X
Participants’ experiences and perceived effectiveness with the Dynamic Work intervention, and their view on essential elements in supporting them to make behavioural changes.		X	X	X								X

*Abbreviations*: *Q-B* Questionnaire participant baseline, *Q-3M* Questionnaire participant 3M, *Q12-M* Questionnaire participant 12M, *FG-3M* Focusgroup participant 3M, *INT-w* Interview withdrawal participant, *AR* Attendance record, *INT-OP-12M* Interview occupational physiotherapist 12M, *FG-HD/TM-12M* Focusgroup head of department/ team manager 12M, *INT-DWc-12W* Interview Dynamic Work coordinator, *FN* field notes reseracher

At baseline participants will be asked how they were attracted to participate in the Dynamic Work intervention and what their reasons were for participation. At follow-up assessments, intervention participants will be asked about their experiences with the Dynamic Work intervention, dose received, perceived effect of the program, and support. Reasons for withdrawal or dropout from the study (measurements) will be registered. Around 3 months after the start of the intervention, from each department 6–8 intervention participants will be invited to participate in a focus group interview to understand: reasons for joining the Dynamic Work intervention, experiences with the Dynamic Work intervention, the impact it has had on their life, their views on essential program elements for making behavioural change, and their suggestions for improvement of the intervention.

At 12 months, all intervention condition heads of departments and team managers will be invited to join a focus group session to gather opinions and experiences with delivery of the Dynamic Work intervention, experiences with recruiting participants for the Dynamic Work study, and barriers and facilitators for adoption, implementation and continuation.

The occupational physiotherapists will be asked to complete attendance and online logs after each team meeting and each on-site department counselling session. The log contains preparation and delivery time, a 10-point scale to score the session, questions on delivery of the intervention, and open-ended questions in terms of what worked and what did not work. At 12 months, all occupational physiotherapists will also be invited for an in-depth interview to gather demographic information, their experiences with (delivering) the Dynamic Work intervention, their view on the essential elements for support in making behavioural change, facilitators and barriers for adoption, implementation and continuation, and their suggestions for changes to the intervention.

Semi-structured interviews will be conducted with the two Dynamic Work coordinators to gather barriers and facilitators for adoption, implementation and continuation, and experiences in recruiting departments for the trial.

Trained researchers (not in direct contact with the occupational physiotherapists, team managers or Dynamic Work coordinators) will use semi-structured interview guides for conducting aforementioned focus groups and interviews. All interviews and focus groups will be audiotaped and fully transcribed verbatim and anonymized.

### Sample size and power calculation

A minimal statistically detectable difference in the primary outcome of 45 min change in total sitting time was chosen. Standard deviations and intraclass correlation (ICC) were based on the results of a previous study in the occupational setting that aimed to reduce sitting time and also used the activPAL as primary outcome measure [10]. To correct for clustering effects within departments and expecting an average of 20 participants per cluster we took an ICC of 0.021 (design effect of 1.40) into account. A standard deviation (SD) of 80.7 was used, with a power of 90%, and alpha of 0.05. Hence, when taking a dropout of 25% into account, sample size of 250 included participants is needed.

### Data handling

All collected data will be kept strictly confidential. All participants will be given a unique ID number, not by name (apart from the consent form). All data will be kept in a secure location within the Amsterdam UMC, location VUmc, accessible only by members of the research team during the active phase of the study; afterwards all data will be archived in line with the policy of VUmc. At the end of the study (i.e. after all final measurements) all participant will receive a digital report of their results (e.g. objectively measured sitting time, standing time, steps, weight, height, and waist circumference) with appropriate explanation. Our university has an internal procedure for auditing ongoing trials for which the current study could be selected. A data monitoring committee is not needed given the fact the intervention is considered low risk. In the unlikely case an adverse event is reported by a participant the principal investigator will be informed. If any adverse event is deemed to be a serious adverse event after consultation with the principal investigator this is reported to the VUmc Medical Ethic Committee within 24 h.

### Statistical analyses

A detailed Statistical Analysis Plan will be developed, and finalized prior to database lock. Data analyses will be conducted after completion of the data collection at 12 months, no interim analysis are planned. Consistent with the cluster-randomized design, multilevel linear regression analyses will be performed according to the intention-to-treat principle with the primary outcome at 12 months as the dependent variable, while study group allocation and baseline value of the primary outcome will be modelled as independent variables. Secondary outcomes will be analysed in a similar way using multilevel linear or logistic regression analyses. Analyses will be performed with multilevel analysis for Windows (MLwiN version 2.22; Centre for Multilevel Modelling, University of Bristol, Bristol, UK) and SPSS version 22 (IBM Corp, Armonk, New York, USA). Statistical significance will be set at *p* < 0.05.

To evaluate the cost-effectiveness of the intervention program statistical analyses will be also done according to the intention-to-treat principle. Missing cost and effect data will be imputed using multiple imputation according to the MICE algorithm developed by van Buuren [38]. Rubin’s rules will be used to pool the results from the different multiply imputed datasets. Bivariate regression analyses will be used to estimate cost and effect differences between intervention and comparison group while adjusting for confounders if necessary. Incremental Cost-Effectiveness Ratios (ICERs) will be calculated by dividing differences in costs between the conditions by the differences in clinical outcomes and Quality-Adjusted Life-Years (QALYs). Clinical outcomes that will be included in the cost-effectiveness analyses are: changes in sitting time, upright time, step counts, BMI, waist circumference, and self-reported physical health. Bias-corrected and accelerated bootstrapping with 5000 replications will be used to estimate 95% confidence intervals around the cost differences and statistical uncertainty surrounding the ICERs. Uncertainty surrounding ICERs will be graphically presented on cost-effectiveness planes. Cost-effectiveness acceptability curves will also be estimated showing the probability that the intervention program is cost-effective in comparison with usual practice for a range of different ceiling ratios thereby showing decision uncertainty [39].

To evaluate the process data of this study descriptive statistics (mean, SD, proportions) will be used to report participants’, occupation physiotherapists’ and departments’ characteristics and results of pre-structured questions from the questionnaires, attendance sheets and coach logs. Descriptive statistics and visualizations will also be used to explore and report the use of the Activator. All reported (suggestions and reasons for) adaptations to the program and any other answers to open-ended questions will be listed, analysed and summarized. A framework analysis approach, following the TCID-framework of Flottorp et al. (2013) [40], will be used to identify barriers and facilitators for adoption, implementation and continuation. Further, we will calculate an ‘implementation score’ by combining specific selected process items reported by participants on delivery or/and dose of the intervention (rated on a five-point Likert scale) [41]. Computing this score will allow us to define low and high implementers and explore differences between departments.

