### Randomisation

Departments are the unit of randomisation, and they will be matched primarily on number of office workers and similarity of work content and tasks. Departments will be randomized into an intervention condition, receiving the Dynamic Work intervention on top of usual practice and a control condition, receiving usual practice only. Possible contamination of the control condition will be avoided as much as possible (e.g. not working on the same floor and not interacting too much with departments in intervention condition on the same or different locations). After baseline data collection, cluster randomisation using a list randomizer (www.random.org) will be performed by a researcher not involved in recruitment or data collection. The result of the randomisation will be shared with the head of the occupational health department of the insurance company, who will inform the heads of the departments and the office workers of the departments.

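### The economic evaluation is specified without a department level although departments are randomised; followed as written, it understates uncertainty for the sitting-time effect, and for costs and QALYs if they cluster

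*Protocol article*

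**What the plan says.** **Randomisation.** The Randomisation section of the protocol article states: "Departments are the unit of randomisation, and they will be matched primarily on number of office workers and similarity of work content and tasks".

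**Sample size.** The calculation allows for clustering: "expecting an average of 20 participants per cluster we took an ICC of 0.021 (design effect of 1.40) into account".

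**Clinical outcomes.** The first analysis paragraph under Statistical analyses gives the design as the reason for the model: "Consistent with the cluster-randomized design, multilevel linear regression analyses will be performed according to the intention-to-treat principle". Secondary outcomes follow the same approach, with multilevel linear or logistic models.

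**Economic evaluation.** The next paragraph sets out a method of its own. Missing costs and effects are imputed by chained equations and pooled by Rubin's rules. Then: "Bivariate regression analyses will be used to estimate cost and effect differences between intervention and comparison group while adjusting for confounders if necessary". For uncertainty: "Bias-corrected and accelerated bootstrapping with 5000 replications will be used to estimate 95% confidence intervals around the cost differences", and the same bootstrap serves the ICERs. Cost-effectiveness planes and acceptability curves follow. The effects entered include changes in sitting time, upright time, steps, BMI and waist circumference, besides QALYs.

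This paragraph carries over intention to treat from the clinical analysis. It does not carry over the multilevel structure, and no other section applies clustering to costs, QALYs or ICERs.

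**The concern.** The unit of randomisation decides which variance belongs in the comparison of arms. If participants in one department resemble each other, a regression or bootstrap that treats them as independent omits the between-department part of that variance, and the intervals come out too short. The protocol accepts this for the clinical outcomes, then names an estimator, an imputation algorithm, a bootstrap type and a replication count for the economic outcomes without a department term in any of them.

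Two things are at stake. Sitting time is both the primary outcome and an effect in the cost-effectiveness analysis, so the text as written would analyse it once with clustering and once without. And cost-effectiveness is a stated aim of the trial, with results meant to inform employers about roll-out. Acceptability curves exist to show decision uncertainty, so a method that leaves out part of that uncertainty would make the evidence look firmer than it is.

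**Working it through.** **1. Does the protocol itself treat clustering as material?**

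Inputs from Sample size and power calculation: difference 45 min, SD 80.7, power 90%, alpha 0.05 (taken as two-sided), ICC 0.021, 20 per department, dropout 25%.

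- Per arm, unclustered: 2 × (80.7 × (1.960 + 1.282) / 45)² = 67.6, rounded up to 68.
- Design effect: 1 + (20 − 1) × 0.021 = 1.399, the protocol's 1.40.
- Total: 2 × 68 × 1.399 = 190; 190 / 0.75 ≈ 254, close to the stated 250.
- Without the design effect: 2 × 68 / 0.75 = 181.

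The stated 250 is therefore reached only with the allowance for clustering.

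**2. What happens if an analysis ignores it?**

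With m participants per department:

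- DE = 1 + (m − 1) × ICC
- factor by which the standard error is understated = √DE
- coverage of a nominal 95% interval = 2Φ(1.96 / √DE) − 1

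Two cluster sizes bracket the case: m = 20 as planned, and m = 20 × 0.75 = 15 after dropout.

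| ICC | m | DE | SE understated by | Coverage |
|---|---|---|---|---|
| 0.021 (protocol, sitting time) | 20 | 1.399 | 1.18 | 90.3% |
| 0.021 (protocol, sitting time) | 15 | 1.294 | 1.14 | 91.5% |
| 0 (assumed) | 20 | 1.000 | 1.00 | 95.0% |
| 0.01 (assumed) | 20 | 1.190 | 1.09 | 92.8% |
| 0.05 (assumed) | 20 | 1.950 | 1.40 | 84.0% |

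Only the ICC of 0.021 comes from the protocol, and it is for activPAL sitting time. The other values are assumptions that show a range for costs and QALYs.

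**3. Simulation check.** Six departments per arm, unpaired, 20,000 runs, ICC 0.021. The interval that ignores departments covered 90.1% (m = 20) and 91.1% (m = 15). A t interval on department means covered about 95% in both.

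**4. What it means on an acceptability curve.** A probability p computed without clustering becomes Φ(z_p / √DE). Assume, for illustration only, that net benefit has ICC 0.021 with m = 20, so √DE = 1.183:

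- p = 0.95: Φ(1.645 / 1.183) = 0.92
- p = 0.90: Φ(1.282 / 1.183) = 0.86

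**5. Number of departments.** 250 / 20 = 12.5, so about 12 departments or six pairs. The 97.5% point of t is 2.23 on 10 degrees of freedom (12 departments, two arms) and 2.57 on 5 (six pairs), against 1.96 for the normal. A department term without a small-cluster correction would therefore still leave intervals too short.

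**The case against.** **The text does not exclude clustering.** A reader might infer that the protocol prescribes an individual-level analysis. It never says so. A bivariate cost-effect regression can hold a department random effect, a bootstrap can resample departments, and an imputation model can include them. The article is condensed and announces a detailed statistical analysis plan. This limits the wording: the independence of participants is inferred from the absence of any cluster term. It does not dissolve the point, because the economic paragraph is not silent on method. It gives a full recipe directly after a paragraph that ties multilevel modelling to the design, and an analyst who followed that recipe would leave departments out.

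**The size is not established for costs and QALYs.** A reader might also infer that every cost, QALY and ICER interval will be too narrow. The documents do not support that. They give no ICC for costs or QALYs, and at ICC 0 nothing is lost. Nor do they promise a separate QALY interval; they promise intervals for cost differences and a display of ICER uncertainty. Desks and counselling are supplied by department, which makes shared variation in programme costs plausible, but that gives no figure.

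**Matching could help.** Departments are paired on size and work content. If the pairing works, it removes between-department variance from the comparison of arms. Neither the formula nor the simulation allows for pairing, so the losses shown may be too large. This stands.

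**The main result is safe.** The primary analysis at 12 months is multilevel and unaffected. This stands too.

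**Conclusion.** The point holds in a limited form. The protocol specifies the economic evaluation without a department level in a trial that randomises departments, and following it as written treats participants as independent.

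- **Sitting-time effect in the cost-effectiveness analysis:** standard errors are understated by about 1.14 to 1.18, and nominal 95% coverage falls to about 90 to 92%. This rests on the protocol's ICC of 0.021, on 15 to 20 participants per department, and on no gain from pairing.
- **Cost intervals, ICER uncertainty and acceptability curves:** the narrowing depends on ICCs that the documents do not give, from none at ICC 0 to about 84% coverage at an assumed 0.05 with 20 per department.

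At the protocol's ICC the distortion is moderate. It is worth correcting because cost-effectiveness is a stated aim and the remedy is cheap.

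**What to change.** State in the statistical analysis plan, before database lock:

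1. **Model.** A bivariate cost-effect model with a department random effect in both equations, or cluster-robust variance, with a small-cluster correction suited to about 12 departments.
2. **Bootstrap, if kept.** Resample at department level in a way that respects the matched pairs. Resampling departments freely within arm would break the pairing. With only about six pairs the bootstrap distribution is coarse, so it also needs the small-cluster correction.
3. **ICER uncertainty.** Build the cost-effectiveness planes and acceptability curves from that model or bootstrap.
4. **Imputation.** Include department in the imputation model, so that imputed values keep the similarity within departments.
5. **Reporting.** Give the estimated ICCs for costs and QALYs, which would settle how much clustering mattered.

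The cost is plan wording, some programming and wider intervals. Recruitment, data collection and the primary analysis do not change.
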